## Abstract

**Background:**

Healthcare and welfare systems worldwide are unprepared to accommodate the growing population of older people. Simultaneously, the cost of reactive care for older people is increasing. However, healthcare systems in many countries are reforming towards integrated and person-centred care with a focus on health promotion and proactive actions. *The Integrating Health Promotion with and for Older People – eHealth (IHOPe)* project aims to describe and evaluate a person-centred e-support intervention that promotes a sustainable partnership between community-dwelling frail older people and health and social care professionals.

**Methods:**

The IHOPe project is designed as a randomised controlled trial comparing a control group receiving standard care with an intervention group receiving standard care and add-on person-centred care through telephone support and a digital platform. The primary outcome measure is a composite score of changes in general self-efficacy and the need for unscheduled hospital care. The project is conducted in Gothenburg, Sweden. At least 220 participants aged ≥ 75 years will be included after being screened using a frailty instrument. The study design, intervention components, digital platform, and questionnaires were developed in close collaboration with an advisory group of inter-professional researchers, stakeholders, clinicians, and older representatives. Data will mainly be collected through questionnaires at baseline and 3, 6, and 12 months after inclusion in the study. Recruitment is ongoing and should be completed during 2023. Data will be analysed using quantitative and qualitative methods. The evaluation will include effectiveness, process, and health economics. The study was approved by the Regional Ethical Review Board in Gothenburg, Sweden (Dnr 2019–05364, Dnr 2020–03550, Dnr 2021–03255).

**Discussion:**

The findings will expand our knowledge of remotely integrated person-centred care for frail older people. Thereby, the IHOPe project is expected to fill highlighted knowledge gaps on intervention evaluations including the triad of person-centred, digital, and integrated care elements, as well as economic evaluations of remote health services for frail older people. The study is ongoing, and the results are not completed but if they turn out to be positive, implementation is not limited to time or location.

**Trial registration:**

ClinicalTrial.gov: NCT04416815. Registered 07/06/2021.

## Background

By 2050, the number of people aged ≥ 75 years is expected to increase by 50% worldwide [1, 2], which means an escalating global demand for diverse healthcare systems [3, 4]. Moreover, the number of people aged > 80 years is also increasing rapidly [1, 2]. Advanced age is often associated with increased risk of frailty, multi-morbidity, and functional impairments [5]. Thus, the development of innovative approaches with health promotive and proactive actions is an urgent need to achieve a sustainable healthcare system that is efficient, equal, and supports health in frail older people [3, 6, 7]. Such approaches should incorporate older people’s capabilities and strengthen a preventive approach in healthcare services, as well as reduce complexity and improve accessibility to health planning and care coordination from the patient perspective [6, 8]. Implementing person-centred care (PCC), utilization of accessible digital health services [2] and teamwork [9] are keystones in such a healthcare system redesign [7, 10]. Several studies show that PCC can be delivered remotely [11] but needs further development for enabling remote teamwork with and for frail older people [12]. Therefore, the project *Integrating Health Promotion With and for Older People - eHealth (IHOPe)* focuses on implementing health planning based on a person-centred ethic [13, 14] and capability approach [15] together with frail older people by working as a team through telephone support and a digital platform.

**Frailty** is a complex syndrome, distinguished from but interrelated to disability and co-morbidity [5, 16, 17]. Frailty is characterised by loss of function and physiological reserve capacity, increased risk of acute illness, falls, disability, institutionalisation, and death [5, 17]. Moreover, frailty in older people is linked to the degree of functional disability regarding their capacity to accomplish daily activities [18, 19]. Frail older people often have more diffuse symptoms than younger people, making diagnosing and identifying underlying symptom causes more difficult. The complexity of detecting frailty in older people can lead to unnecessary emergency visits, as the underlying cause of the health disruption has not been addressed. Identifying frail older people where the need for emergency care could be prevented by frailty screening is necessary to decrease the high number of emergency care visits in this patient group [16, 20].

PCC emphasises the relationship between the healthcare professional (HCP) and the older person as a prerequisite for shared decision making in health planning and successful care [21]. In line with our previous research, person-centred telephone support can be seen as a promising tool to initiate health planning with older people [11]. In addition, digitally shared documentation indicated an increase in self-efficacy [22, 23]. Self-efficacy, defined as a person’s belief that they can successfully execute behaviours necessary to achieve desired health goals [24], has been proposed as a central concept in PCC [25]. PCC aims to co-create patients’ self-efficacy rather than convince or educate them about the value of such behaviours [14, 24]. Three key components in implementing PCC in daily clinical practice are formulated to build self-efficacy [14]. The first step is to initiate the partnership by capturing patients’ narratives and experiences of their opportunities and barriers in everyday life. The next step is to work the partnership between patients and HCPs through discussion and shared planning of care and treatment. The last step is safeguarding the partnership by documenting the patient’s preferences, beliefs, values, and agreement on future planning [14]. These three steps of initiating, integrating, and safeguarding the partnership are incorporated into this project to operationalise PCC.

Person-centred teamwork involves the older person as an equal partner in the health care team, in which HCPs work *with* the older person (and often with significant others) [9]. Previous research on supporting frail older people has had their point of departure in existing healthcare teams (usually situated within social and healthcare organisations) [26–29]. In addition, the patients and their significant others have not been described as team members. The need to engage frail older people as equal partners in the healthcare team has been recently highlighted [9]. The partnership-building process may be facilitated through person-centred telephone support and an accessible digital platform. Our research has shown that working in partnership remotely is possible and efficient [11, 30]. To our knowledge, no previous research has investigated the effectiveness of such support among frail older people. The innovative aspect of this study is the remote use of a preventive strategy by co-created health planning between frail older people and their health and social care team. The underlying hypothesis is that working in partnership through telephone support and the opportunity to communicate with HCPs via the digital platform is a feasible and effective use of available resources. Such an intervention will lead to reduced hospital admissions and postpone a decrease in self-efficacy in frail older persons. In addition, the project will expand our knowledge about if and how a remotely person-centered intervention can contribute to bridging the digital exclusion experienced by frail older people in many of today’s eHealth solutions [31, 32].

## Aim

The **IHOPe** project aims to evaluate the effects, describe the process, and perform a health-economic evaluation of a person-centred remote intervention to promote a sustainable partnership between community-dwelling frail older people and health and social care professionals.

**Specific aims**:

To evaluate the preventive effects of a remote person-centred support on self-efficacy and hospitalisation of community-dwelling frail people ≥ 75 years.To describe, through a process-evaluation, the applicability, feasibility and reach of remote PCC.To explore and evaluate frail older peoples’ experiences of a remote person-centred intervention.To perform a health economic evaluation of the remote PCC intervention compared to usual care.

## Methods and design

The IHOPe study will be designed as a randomised controlled trial (RCT) with two parallel groups and a primary endpoint assessed three months after inclusion. In addition, the IHOPe project will include health economic and process evaluations. The project will be a complex intervention and, as such, features a multitude of influencing factors [33]. The study design will be guided by the revised Medical Research Council’s (MRC) framework for complex interventions [34] and the guidelines for reporting parallel group RCTs [35]. We opted for the updated version of the original MRC framework due to its iterative approach and increased focus on early-phase piloting and development of the complex intervention [34]. The IHOPe project will consist of two phases corresponding with the three steps of *Development and Feasibility and Piloting* and *Evaluation* of the MRC framework. The *implementation* steps will be planned throughout the project. This manuscript presents the RCT.

Phase 1: Develop and test the feasibility of a person-centred e-support intervention and pilot the RCT design.

Phase 2: Evaluate the effects, describe the process, and perform a health economic evaluation of the person-centred e-support intervention.

### Patient and public involvement

The involvement of different categories of knowledge users (e.g. older people, health professionals and decisionmakers) is advocated as a crucial part of research [36, 37]. Therefore, the planning and designing of the study have been conducted in close communication and collaboration with an advisory group including older people, inter-professional researchers, decisionmakers, and clinicians. The development of the digital platform was guided by a participatory design [38]. Moreover, the entire study, including recruitments, choice of instruments, questionnaire development, and the intervention components, have been, and continually will be, co-created with the advisory group.

Participants and setting.

The IHOPe project will be conducted in Sweden and targets community-dwelling older people aged ≥ 75 years, their families, and professionals working in social and healthcare services. Sweden has an ongoing redesign of healthcare services towards person-centred integrated care, which aims to strengthen primary care services and self-care [10]. Health costs in medical care are mainly financed through taxes, where municipalities are responsible for services for older people according to assessed needs. Several actors could be involved in formal care activities for frail older people representing different health and social care organisations. There is also an option to seek private health and social care providers [10]. In addition, it is common that older people are receiving support or help from informal caregivers [3, 10]. Therefore, the evaluation process also includes significant others and HCPs invited to the IHOPe platform. All participants must provide signed informed consent before any study procedures occur.

#### Inclusion criteria

Inclusion criteria will be national registration within the Region Västra Götaland, men and women aged ≥ 75 years living in ordinary housing and screened as frail at an emergency department but not hospitalised.

#### Exclusion criteria

Exclusion criteria will be those needing palliative care in the final stages of life, no registered address, participating in a conflicting randomised study, or cognitive dysfunctionality (not oriented to time, place, and person).

### Enrolment and randomisation

Frail older people will be recruited from the emergency department at a university hospital in Gothenburg, Sweden, to include a diverse population of frail older people. The planned flow of participants is shown in Fig. 1.

**Fig. 1 Fig1:**
[figure not shown]
Flow chart of participant enrolment, allocation, follow-up, and analysis [35]

Participants aged ≥ 75 years will be screened using an instrument developed by the Frail Elderly Support Research Group (FRESH) [39] as part of usual care at the emergency department or by a research assistant via telephone. The screening results (if frail or not) will be documented. The research assistant will screen patients identified as frail for eligibility to participate in the study using the above-mentioned inclusion and exclusion criteria and the electronic patient record. A study information letter and invitation to participate will be sent to eligible patients within two weeks after their emergency visit. The patient will then be contacted by telephone to provide verbal information and asked about consent to participate. Finally, written participant information and informed consent forms will be sent to patients willing to participate.

All who fulfil the inclusion criteria and consent to participate will be randomised into the study. Participants will be randomly assigned to the control or the intervention group with a 1:1 allocation using a computer-generated randomisation schedule. The control group will receive usual care whilst the intervention group will receive the person-centred e-support intervention for six months in addition to usual care.

The recruitment of participants to the main study started after the inclusion of 17 participants in a pilot study. The full-scale RCT is currently ongoing. Follow-up for each study participant continues for 12 months from inclusion.

Recruitment of significant others and HCPs depart from the older people’s network by contact information to significant others or formal carers invited to the intervention.

### Control group

The participants allocated to the control group will receive *usual care*. Routine care for older people in Sweden includes care delivered by diverse HCPs in hospital, primary care, municipal, and home care services. Also, informal carers are often involved. It is unusual to have any follow-up contact from the emergency ward for frail older people who are not admitted to hospital. However, within usual care some patients are contacted by a ‘mobile team’ (consisting of nurses and physicians) through a coordinator at the emergency ward. The mobile team visits the patient at home or contacts the municipal care provider for further follow-up, depending on the older person’s healthcare needs and status [40]. However, the mobile team does not deliver digital healthcare.

### Intervention group

In addition to usual care, participants allocated to the intervention group will receive person-centered telephone support and the opportunity to communicate with HCPs through the digital platform for six months. The intervention is delivered remotely and is coordinated by dedicated registered nurses (RNs). The HCPs conducting the intervention receive continuous training through workshops with specialists in PCC, ethics, communication, and pedagogics on how to apply remote PCC.

Intervention components.

The intervention aims to initiate partnership-building, encourage older people to describe their health situation and needs, and further identify and engage their capabilities and resources [43].

### Telephone support and the creation of a health plan

An HCP will initiate the first telephone conversation shortly after study inclusion (within two weeks). After the first telephone call, a follow-up appointment will be mutually planned and agreed upon between the HCP and the older person. In addition, there is the opportunity for incidental contact with the older person by telephone or through the digital platform. The participants’ narrative of their everyday situation, as well as their needs, resources, and health-related goals are the core components of the telephone conversations [11, 41]. The conversation will start with recapitulating the aim of PCC support, asking open-ended questions, and listening to the participants’ experience of their condition, context, needs, and resources. The HCP will confirm and summarise the content of the conversation and, in collaboration with the participant, co-create achievable and relevant health-related goals. The participants’ narratives (at times in partnership with significant others), goals, and strategies to manage everyday life, as well as needs of support and actions and resources to achieve agreed health-related goals, will then be documented in a health plan by either the participant or the HCP and uploaded to the digital platform. This health plan is, however, a living document and can be modified and reformulated during the intervention, as is described in other PCC projects with different populations [22, 42, 43].

### The digital platform

The digital platform has been tested in previous studies and the present study will apply the same procedure of working together via the platform [22, 43]. All participants are invited to communicate on the platform. The participants or the responsible HCP will upload the mutually agreed health plan to the digital platform. Depending on agreements during the phone call, family, friends, and additional health professionals may be invited to join the digital platform team. An HCP will introduce and explain how to use the digital platform and create a personal account. The platform is a mediator through which the participants, together with their team (i.e., formal and informal family and informal carers), can develop the health plan and follow-up actions and goals. The platform allows self-monitoring through daily ratings on a scale from 1 to 5 on symptoms and general well-being (e.g., how well they have slept). In addition, the participants and the HCPs can communicate through messages in a chat-like forum. The platform will contain an assembly of links to other relevant web pages that the participants can use to seek information or connections. HCPs log into the platform on weekdays to be updated on patients’ activities and check for messages [22, 43]. If signs of deterioration occur needing for example changes in the pharmacological treatment, the participants will be advised to contact their primary care physician and if symptoms then are assessed as urgent, they are encouraged to contact the emergency healthcare services.

### Data collection

Various data sources will be used, including questionnaires (see detailed description in Table 1), activities performed by the participants in the digital platform, time consumption during conversations, and for writing health plans and medical records. In addition, the selection of participants (in the intervention group), as well as significant others and health professionals invited for teamwork, will be asked if they are willing to participate in focus groups or individual interviews. Clinical and self-reported data (e.g., questionnaires) will be collected at baseline and after 3, 6, and 12 months. The primary and secondary endpoints have been used in large national or international studies and tested for validity and reliability [42, 44]. Moreover, register data will be collected retrospectively from the National Board of Health and Welfare: each registered holder, health care encounters from the regional patient register VEGA [45], use of prescribed drugs dispensed in outpatient pharmacies from the Swedish Prescribed Drug Register (SPDR) [46], use of home help services and supported living facilities, municipal health care use, and information about potential causes of death.

### Outcomes and measurements

Questionnaire data will be gathered at baseline and after 3, 6, and 12 months from the inclusion date. Self-reported baseline characteristics of the participant’s sex, age, civil status, country of birth, and level of education will be collected through questionnaires at baseline.

### Primary outcome

In line with previous RCTs evaluating PCC [22, 43] the primary outcome will be a composite of clinical changes [47], in general self-efficacy and the need for hospital care for unscheduled reasons after 3 months. Each participant will be classified as improved, deteriorated, or unchanged at three months as follows:

*Deteriorated*: the participant’s general self-efficacy has decreased by $$\ge$$5 units or has been admitted to hospital for unscheduled reasons two or more times.*Improved*: general self-efficacy has increased by $$\ge$$5 units, and the participant has not been admitted to hospital more than once.*Unchanged*: the patient has neither deteriorated nor improved.

### Secondary outcomes

A composite of changes in general self-efficacy [48, 49] and the need for hospital care for unscheduled reasons at 6 and 12 months.

#### General self-efficacy

The General Self-Efficacy Scale (GSES) [48, 49] is a 10-item self-assessment psychometric questionnaire designed to measure a broad and stable sense of personal competence to deal with stressful situations. Ratings are made on a 4-point Likert scale (1 = not at all true, 2 = hardly true, 3 = moderately true, 4 = exactly true) and are summed to give a total score ranging from 10 to 40, with higher scores indicating generalised greater self-efficacy. The GSES has been validated in several languages. An increase of 4.6 units in the total score has been proposed and is used as a limit for a minimally important difference [11, 22, 41].

#### Hospitalisation

Hospitalisation refers to the number of unplanned emergency department visits and hospital admission according to patients’ self-reported responses (questionnaires) and data in medical records.

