#### Frailty according to the clinical Frailty Scale (CFS) version 1.2

The degree of frailty will be assessed from 1 to 9; 1: very fit, 2: well, 3: manging well, 4: vulnerable, 5: mildly frail, 6: moderately frail, 7: severely frail, 8: very severely frail, 9: terminally ill) [69].

For details about primary and secondary outcomes, data sources, and time points for data collection, see Table 1.

**Table 1 Tab1:** Overview of primary and secondary outcomes, demographic measures, data sources, and time points for data collection

	Research assessment/data source/register data	T0 baseline	T1 3 months	T2 6 months	T3 12 months	Retrospectively collected
Primary outcomes						
A composite of clinical changes in general self-efficacy and the need for hospital care for unscheduled reasons at 3 months	Questionnaires	x	x			
	Medical records from baseline up to 3 months and register data					

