**Secondary outcomes**						
A composite of changes in general self-efficacy and the need for hospital care for unscheduled reasons at 6 and 12 months	Questionnaires	x		x	x	
	Medical records from baseline up to 12 months and register data					
Health-related quality of life	Questionnaires	x	x	x	x	
Capability-related quality of life according to ICECAP-O	Questionnaires	x	x	x	x	
Hospitalisation	Questionnaires, Medical records					x
General self-efficacy	Questionnaires	x	x	x	x	
Change in ability to perform activities of daily living according to the ADL staircase	Questionnaires	x	x	x	x	
Societal costs	Register data, Questionnaires, Digital platform data, and Communication lists.					x
Incremental cost-effectiveness ratio	Questionnaires Registers	x	x	x	x	x
Change in the burden of medicine use in everyday life according LMQ-3	Questionnaires	x	x	x	x	
Change in the participants’ self-rated overall level of burden of medicine	Questionnaires	x	x	x	x	
Social network, social support, and loneliness five questions	Questionnaires	x	x	x	x	
**Demographics**		x				
Background questions, six questions	Questionnaires	x				
Self-reported frailty according to the TFI	Questionnaires	x				
Frailty according to CFS	Researchers’ objective assessment	x				

ICEpop CAPability measure for Older people (ICECAP-O), Activities of Daily Life (ADL), Living with Medicines Questionnaire version 3 (LMQ-3), Tilburg Frailty Indicator (TFI), Clinical Frailty Scale (CFS).

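### The improved rule of the primary composite counts planned as well as unscheduled admissions, and the article does not say whether emergency department visits stay out of the composite

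*Protocol article*

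**What the plan says.** **Name of the component.** The Primary outcome section calls the hospital half of the composite "the need for hospital care for unscheduled reasons after 3 months". The abstract uses the similar label "changes in general self-efficacy and the need for unscheduled hospital care".

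**Classification rules (Primary outcome).**
- Deteriorated: self-efficacy falls by at least 5 units, or the participant "has been admitted to hospital for unscheduled reasons two or more times".
- Improved: self-efficacy rises by at least 5 units, and "the participant has not been admitted to hospital more than once".
- Unchanged: "the patient has neither deteriorated nor improved".

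**Measurement description.** The Hospitalisation subsection, which comes after the Secondary outcomes heading, reads "Hospitalisation refers to the number of unplanned emergency department visits and hospital admission" and names patient questionnaires and medical records as sources. Table 1 gives Hospitalisation its own row among the secondary outcomes ("Questionnaires, Medical records"). For the primary composite, Table 1 lists questionnaires and, in addition, "Medical records from baseline up to 3 months and register data".

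**Power.** The Sample size section dichotomises the composite: improved or unchanged, 20% against 40%, 80% power, p-value 0.05, 91 per group required and 110 planned.

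**The concern.** The two hospital rules in the same definition count different things. Deteriorated is limited to unscheduled admissions; improved is not. Planned care lies outside the construct the component is named for, yet as written it can take the improved category away from a participant who met the self-efficacy threshold. If the same rules serve the 6- and 12-month composites, the longer windows leave more room for planned stays.

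The second issue is an open question of scope. The first specific aim speaks of hospitalisation, and the only place that term is defined counts unplanned emergency department visits along with admissions. The self-efficacy description has the same position in the article (after the Secondary outcomes heading, with its own secondary row in Table 1), yet it plainly describes a component of the primary composite. An analyst could treat the Hospitalisation description in the same way. The article neither tells the analyst not to, nor says how to count a visit that ends in admission. That choice would affect who is deteriorated, and so the powered outcome.

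**Working it through.** **1. The plan's own figure.** Inputs from the Sample size section: 0.20 and 0.40, 80% power, p-value 0.05 (taken as two-sided; sidedness is not stated).

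Pooled normal formula: n = [1.960·√(2·0.30·0.70) + 0.842·√(0.20·0.80 + 0.40·0.60)]² / 0.20² = [1.270 + 0.532]² / 0.04 ≈ 81.2, so 82.

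Continuity correction: (81.2/4)·[1 + √(1 + 4/(81.2·0.20))]² = 20.3·(2.116)² ≈ 90.9, so 91.

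The stated 91 reproduces. The arithmetic is not in question.

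**2. The improved rule.** Take a participant whose self-efficacy rises by at least 5 units, with *u* unscheduled and *p* planned admissions by 3 months.

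| u | p | As written | With the unscheduled limit in both rules |
|---|---|---|---|
| 0 | 0 | improved | improved |
| 0 | 1 | improved | improved |
| 1 | 0 | improved | improved |
| 0 | 2 | **unchanged** | improved |
| 1 | 1 | **unchanged** | improved |
| 2 or more | any | deteriorated | deteriorated |

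The rules disagree when u ≤ 1 and u + p ≥ 2. A single planned stay does no harm. With the limit in both rules, the two hospital conditions become exact complements (u ≤ 1 and u ≥ 2).

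Every affected participant moves from improved to unchanged. Both belong to the improved-or-unchanged group, so the 20%, the 40% and the 91 stay as they are. Only the three-category result, or any analysis of improved on its own, is affected.

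**3. The emergency department count.** On the literal Primary outcome rules, a visit that ends in admission is one admission and does not meet the threshold of two. If the Hospitalisation count were used instead, and the visit and the admission were each counted, the same episode would be two events and would meet it.

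The documents give no admission or visit rates, so what follows is illustration only. Assume that a share *q* of otherwise non-deteriorated participants, equal in both arms, has one such episode and is reclassified as deteriorated. The proportions become 0.20(1 − q) and 0.40(1 − q).

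| q | Control | Intervention | n per group (continuity-corrected) | Power at 91 per group (uncorrected) |
|---|---|---|---|---|
| 0 | 0.20 | 0.40 | 91 | 0.84 |
| 5% | 0.19 | 0.38 | 98 | 0.82 |
| 10% | 0.18 | 0.36 | 106 | 0.79 |
| 20% | 0.16 | 0.32 | 123 | 0.72 |
| 30% | 0.14 | 0.28 | 146 | 0.64 |

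To relate q to a rate, assume further that admissions are Poisson with mean λ per 3 months, are independent of self-efficacy, and all come through the emergency department. Among people with fewer than two admissions, the share with exactly one is λ/(1 + λ): 9% at λ = 0.1, 17% at 0.2, 29% at 0.4. Applied to the 20% and 40%, the composite shifts by about 2 points (0.20 × 9%) to 11 points (0.40 × 29%). Repeat visits without admission would add to this.

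**The case against.** The best reply on emergency department visits is that the primary outcome has its own rules, and both are worded in terms of being admitted. The sentence that counts visits describes an outcome listed separately as secondary, and the Background states the hypothesis as fewer hospital admissions. This largely stands. A reader might infer that the article defines the primary outcome in two contradictory ways; it does not. Double counting needs two steps that the text never states: carrying the secondary count into the composite, and counting a linked visit and admission as two events. The abstract is not a third definition either, since it repeats the label used before the rules are given. What remains is that the article does not close the other reading.

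On planned stays, the reply is that the opening sentence already limits the component to unscheduled care, so the missing words may be simple shorthand. That may be what was meant. But one rule carries the limit and the next does not, and followed literally they give different categories.

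On data sources, a reader might infer that the primary outcome depends on self-report from unblinded participants. Table 1 does not support this: it assigns medical records and register data to the composite, and questionnaires are needed there for self-efficacy in any case. Only the order of precedence is unstated.

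Finally, counting linked episodes is a detail that an article may leave to the full protocol or analysis plan. That is fair, and it is one reason to treat the second issue as a clarification.

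**Conclusion.** The mismatch between the improved and deteriorated rules is certain from the text and should be corrected. Its reach is limited: it takes at least two admissions in total with fewer than two unscheduled, it moves participants only from improved to unchanged, and it leaves the powered proportion and the sample size untouched. How many participants it affects cannot be computed, because no rates of planned admission are given.

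The emergency department issue is an ambiguity. If it were resolved towards the secondary count, it would affect the powered outcome, but the documents do not allow its size to be estimated. The figures above depend on assumed rates and on that reading. A starker contrast is tempting: at an assumed 0.2 admissions per 3 months, 1.8% of participants have two or more and 18% have at least one. That contrast looks at the admission component alone. Only the 20% to 40% assumed to be improved or unchanged can be newly reclassified, so the shift in the composite is smaller. Nor do the documents show that any choice of definition will be made after seeing the data.

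This is a wording correction worth making before analysis. It does not show that the primary outcome is unusable.

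**What to change.** 1. Add the restriction to unscheduled reasons to the improved rule, so that both hospital conditions count the same events.
2. State that the composite at 3, 6 and 12 months counts unscheduled inpatient admissions only, as the Primary outcome rules already say for 3 months. An emergency department visit that leads to admission is part of that admission, and the emergency department count stays with the secondary Hospitalisation outcome.
3. State that, for the hospital part of the composite, the medical records and register data already listed in Table 1 take precedence over self-report.

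The cost is a few words in the outcome section and the same words in the analysis plan. The data are already being collected, and the sample size does not change.
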